### Sample size

For the primary objectives of efficacy, tolerability, and adherence, the sample size was calculated using G*power 3.1 [56] using a 2 (groups) × 2 (time) repeated-measures ANOVA. Given the active control condition, we expect a medium effect size [9]. For a between group effect size of f = 0.25, alpha 0.05, power 0.80, 0.5 correlation among repeated measures and 1.0 non-sphericity correction, a total sample size of 98 participants is needed for two-sided testing. Although no formal method is available to determine a repeated-measures ANOVA sample size using Bayesian statistics, approximations for t-test are available [57]. For a one-sided *t*-test with a power of 0.80 and a Bayes factor of 3 (indicating evidence for the data coming from the alternative than the null hypothesis), 87 participants are needed and for a Bayes factor of 5, 99 participants are needed. Originally, we aimed to recruit 100 participants (see pre-registration: ISRCTN - ISRCTN29668369). However, the COVID-19 pandemic has seriously impacted the number of referrals of patients with panic disorder. To increase the feasibility of the study, we formulated directional hypotheses and decided to use one-sided testing, which reduces our sample size to 50 participants [58]. This change was approved by the ethical committee on February 8 2023. Participants who will not show up to therapy sessions in the first two weeks of treatment will be considered non-compliant and will be described as dropouts. Dropouts will not be excluded from intent to treat analyses, but will be replaced by additional participants to preserve statistical power. The completer sample size will be sufficient to address secondary objectives.

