Secondly, we expect to recruit a culturally and socioeconomically diverse sample. No strict exclusion criteria are used and clinics are in large cities across the Netherlands, which enhances the external validity of our results [119, 120]. Given that dropouts are common in this population [11–14], we will use an intention to treat analysis. Reasons for dropout will be monitored as attrition rates are an important outcome measure in this study. Validity of the trial is further improved by using standardized measures and by letting the assessments being conducted by researchers blind to treatment condition. Furthermore, the sample size should provide sufficient power for the primary- and secondary aims to enable meaningful conclusions.

Researcher allegiance bias is problematic in psychotherapy research [121, 122], including studies about EMDR therapy efficacy in anxiety disorders [38, 40]. Therefore, we follow recommendations to reduce research allegiance bias, such as having a collaborative team with mixed allegiances [121]. Study therapists are trained and supervised for the same amount of time for all treatment conditions, and treatment integrity will be checked [123]. To reduce expectancy biases in patients and clinicians a strong rational for all treatments, including supportive counselling, is provided. Furthermore, we use identical procedures (including EMDR-case conceptualization) and treatment duration between conditions. Treatment credibility and expectancy for all treatments are monitored for all patients and study-therapists.

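### The Bayesian sample sizes of 87 and 99 match numbers per arm but are presented as trial totals; the totals would be 174 and 198

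*Protocol article*

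**What the plan says.** The protocol article, Sample size, starts from a repeated-measures ANOVA: "For a between group effect size of f = 0.25, alpha 0.05, power 0.80, 0.5 correlation among repeated measures". With no non-sphericity correction it concludes that "a total sample size of 98 participants is needed for two-sided testing". It then turns to a Bayesian approximation: "For a one-sided *t*-test with a power of 0.80 and a Bayes factor of 3", the requirement is "87 participants are needed and for a Bayes factor of 5, 99 participants are needed". The next sentence gives the original aim of 100 participants. After describing the fall in referrals, the section reports the present target: "we formulated directional hypotheses and decided to use one-sided testing, which reduces our sample size to 50 participants". The Discussion adds that "the sample size should provide sufficient power for the primary- and secondary aims to enable meaningful conclusions".

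The Bayesian sentence carries no per-group label. It does not repeat the effect size or name the type of Bayes factor or its prior.

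**The concern.** The figures 87 and 99 follow a number explicitly called a total and lead directly to a recruitment target of 100, so a reader takes them as totals. They look too small for that. Under a one-sided two-sample t-test at a medium effect, the ordinary 5% test already needs more than 100 patients, and a Bayes factor above 3 is a harder threshold than p < 0.05.

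These are the only explicit one-sided calculations in the article, and they stand just before the claim that one-sided testing allows 50 patients. If they are per-arm numbers, the section suggests that about 100 patients would give an 80% chance of a Bayes factor above 5, which they would not. It also makes the step down to 50 look smaller than it is.

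**Working it through.** **Inputs from the Sample size section.** One-sided t-test; power 0.80; thresholds 3 and 5; f = 0.25; correlation 0.5 between two measurements. The trial has two parallel arms.

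**Assumptions.**
- The medium effect carries over to the t-test: d = 2f = 0.5.
- Allocation is 1:1.
- The Bayes factor is the approximate adjusted fractional one with the minimal fraction, b = 1/(2n) for n per arm.

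**The neighbouring frequentist figure.** For the between-group effect, λ = f²·N·m / (1 + (m − 1)ρ) with m = 2 and ρ = 0.5. At N = 98, λ = 0.0625 × 98 × 2 / 1.5 = 8.17 and two-sided power is 0.808. The 98 reproduces, and it is a total.

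**The Bayesian figures.** For the null against a directional alternative,

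BF = 2Φ(t) · √b · exp(t²/2).

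Solve BF = threshold for the critical t. Then take the probability of exceeding it from the noncentral t with 2n − 2 degrees of freedom and noncentrality d√(n/2).

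- BF 3, n = 87 per arm: b = 1/174 and critical t = 2.446 (check: 1.986 × 0.0758 × 19.93 = 3.00). Noncentrality is 0.5 × √43.5 = 3.30. Probability **0.802**; n = 86 gives 0.797.
- BF 5, n = 99 per arm: b = 1/198 and critical t = 2.670 (check: 1.992 × 0.0711 × 35.31 = 5.00). Noncentrality is 0.5 × √49.5 = 3.52. Probability **0.801**; n = 98 gives 0.796.

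Both printed figures are matched to the integer as numbers **per arm**. At these sizes the mirror criterion also holds: the probability of equally strong evidence for the null, when it is true, is 0.907 and 0.843. Of the ten d values tried between 0.3 and 0.8, only 0.5 gives the pair 87 and 99 (for example, 0.45 gives 111 and 126; 0.55 gives 70 and 80). Totals: 2 × 87 = **174** and 2 × 99 = **198**.

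**What various totals deliver at d = 0.5:**

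| Total | Per arm | P(BF > 3) | P(BF > 5) |
|---|---|---|---|
| 87 | 43–44 | 0.51–0.52 | 0.43–0.44 |
| 99 | 49–50 | 0.56–0.57 | 0.48–0.49 |
| 100 | 50 | 0.57 | 0.49 |
| 50 | 25 | 0.35 | 0.27 |

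For 87 and 99 to be totals at probability 0.80, d would have to be about 0.67 to 0.68.

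**Does the choice of Bayes factor matter?** A one-sided half-Cauchy prior with scale 0.707 needs 73 per arm for BF 3 and 87 for BF 5 (146 and 174 in total); a normal approximation to the likelihood gives 86 instead of 87. Larger fractions in the fractional Bayes factor (two or three times the minimum) need at least 73 per arm for BF 3 and 86 for BF 5. No two-sample variant tried gives 87 and 99 as totals.

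**Benchmark without a Bayes factor.** The ordinary one-sided 5% t-test at d = 0.5 has power 0.799 with 50 per arm and 0.806 with 51, so it needs 102 in total. At 44 per arm its critical t is 1.66, against 2.30 for BF 3.

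**The case against.** The article does not give the effect size, type of Bayes factor or prior for this calculation, and the cited method paper is not at hand. The word total is attached only to 98. The per-arm reading is therefore an inference, and 174 and 198 are conditional on the assumptions above. That is correct. But two figures matching to the integer under one setting is unlikely to be chance, and every two-sample alternative tried at a medium effect also rules out the totals.

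The benchmark of 102 is also open to challenge. The section's own model averages two measurements, and tested one-sided it needs only 76 in total (power 0.802), which is below 87. So 102 alone does not exclude the printed figures. Crediting that gain does not rescue them, though. Averaging raises the effect to 0.5/√0.75 = 0.577, and the fractional Bayes factor then needs 63 and 72 per arm, or 126 and 144 in total.

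Finally, the current target of 50 is attributed to directional hypotheses and another reference, not to 87 or 99, and the Data analysis section mentions no Bayes factor. This limits the consequence: correcting the figures changes no target, decision rule or planned analysis. It does not make the printed figures right. Whether one-sided testing justifies 50 is a separate question that this point does not settle.

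**Conclusion.** The sentence is wrong as written. At the section's medium effect, 87 and 99 are numbers per arm, and the corresponding totals are 174 and 198. Read as totals, they give a probability of about one half instead of 0.80. The Bayesian figures therefore did not support the original target of 100 (0.57 for BF 3, 0.49 for BF 5), and they support 50 still less (0.35 and 0.27).

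The exact totals rest on d = 0.5 and the fractional Bayes factor with minimal fraction. The conclusion that 87 and 99 are too small as totals does not depend on which of the tried Bayes factors was used. It would fail only if a clearly larger effect, about 0.68, had been assumed, and the section does not say so.

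**What to change.** - Restate the figures as 87 per group (174 in total) for a Bayes factor of 3 and 99 per group (198 in total) for 5, after checking them against the original calculation.
- State the effect size, the type of Bayes factor and its prior or fraction.
- Add what 50 patients deliver on the same basis (about 0.35 and 0.27 under the assumptions here), or remove the sentence as support for the sample size.
- Bring the Discussion's statement on sufficient power into line with the corrected figures.
- While the calculation is open, check whether 50 is also a per-group number. A one-sided t-test at d = 0.5 has power 0.80 with 50 per arm and 0.54 with 25 per arm. This is only a possibility; the document does not show how 50 was derived.

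The cost is wording only. Design and analysis do not change, but the stated justification becomes less favourable.

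### One-sided testing alone takes the planned 98 participants to 76, not 50; on the stated inputs, 50 gives about 64% power rather than 80%

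*Protocol article*

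**What the plan says.** The Sample size section of the protocol article names its method: "the sample size was calculated using G*power 3.1 [56] using a 2 (groups) × 2 (time) repeated-measures ANOVA". Its inputs are "f = 0.25, alpha 0.05, power 0.80", with a correlation of 0.5 between repeated measures and a non-sphericity correction of 1.0. From these it concludes that "a total sample size of 98 participants is needed for two-sided testing".

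It then reports that COVID-19 reduced referrals and that, to make the study more feasible, "we formulated directional hypotheses and decided to use one-sided testing, which reduces our sample size to 50 participants". A reference is cited at that point, but no new effect size, alpha, power or correlation is given. The Protocol version section describes the same amendment (100 to 50) and names the move from two-sided to one-sided testing as the only statistical change.

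The Discussion still says that "the sample size should provide sufficient power for the primary- and secondary aims to enable meaningful conclusions".

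**The concern.** For a single two-group contrast, moving alpha 0.05 into one tail at 80% power usually saves a little over a fifth of the sample. Here the total falls by almost half (98 to 50), and the text presents this as the result of one-sided testing.

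If 50 does not follow, the amended paragraph gives a wrong derivation for the number on which the reduced trial rests. The Discussion's assurance on power then has no calculation behind it. A reader judging a non-significant result would take the type II error to be near the planned 20%, when on the stated inputs it is about 36% for the sizing test.

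**Working it through.** **Inputs (Sample size section).** Two groups, m = 2 times, between-group f = 0.25 (d = 2f = 0.5), alpha 0.05, power 0.80, correlation ρ = 0.5, non-sphericity 1.0. Equal allocation is assumed, in line with the balanced distribution described under Randomization.

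**Formula (repeated-measures ANOVA, between factors).** Noncentrality λ = f² × N × m / (1 + (m − 1)ρ) = 0.0625 × N × 2 / 1.5 = 0.0833N, referred to F(1, N − 2). The one-sided version is a noncentral t with N − 2 degrees of freedom and noncentrality √λ.

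**Step 1: reproduce the plan's figure (two-sided, alpha 0.05).**
- N = 96: λ = 8.00, power 0.799.
- N = 98: λ = 8.17, power 0.808.

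The smallest even total reaching 0.80 is 98, as stated, so the method is identified.

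**Step 2: change only the sidedness (one-sided, alpha 0.05).**
- N = 74: λ = 6.17, power 0.792.
- N = 76: λ = 6.33, power 0.802.

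The one-sided total is 76. The reduction is (98 − 76)/98 = 22%; the reduction claimed is (98 − 50)/98 = 49%.

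**Step 3: power at N = 50.** λ = 4.17, √λ = 2.04. Power is 0.643 one-sided (0.516 two-sided). For 80% one-sided power at N = 50, f must be about 0.309 (d about 0.62), or one-sided alpha about 0.118. Neither is stated.

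**Step 4: the planned type of analysis.** The Data analysis section plans a mixed regression with baseline as covariate. In units of the outcome variance:
- *Single time point (T2 or T3).* The variance factor is 1 − ρ² = 0.75. This equals (1 + ρ)/2 = 0.75 in the sizing ANOVA, so the noncentrality is again 2.04. With 47 degrees of freedom, power is 0.643.
- *Common effect pooled over T2 and T3.* The mean of the two has variance 0.75 and covariance 0.5 with baseline, so the factor is 0.75 − 0.25 = 0.50. Noncentrality is 0.5 × √(50/(4 × 0.50)) = 2.50 and power is 0.79. N = 52 gives 0.81.

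**Step 5: intention-to-treat size.** Recruitment continues until 50 complete T3, and dropouts are replaced but kept in the intention-to-treat set. The Background cites 10–20% dropout. Assuming that range applies here, 50/0.9 to 50/0.8 gives roughly 56 to 62. Single-time power is then 0.69 (N = 56) to 0.73 (N = 62), before any dilution of the effect.

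**Step 6: could another reading of the same inputs give 50?** The group-by-time interaction needs 34 two-sided and 28 one-sided. An unadjusted t-test at d = 0.5 needs 126 and 100 by normal approximation. Neither gives 98 or 50. The pooled baseline-adjusted effect comes close to 50, but the text does not give it as the source, and it is not the calculation that produced 98.

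**The case against.** The strongest reply is that 64% is the power of the sizing ANOVA, not of the trial. The planned model uses baseline as a covariate and could use both T2 and T3. At the stated correlation, a pooled effect has about 79% power with 50 participants. The intention-to-treat set will also probably exceed 50. Both points stand, so power has to be quoted for a named contrast. They do not rescue the derivation. The text attributes 50 to one-sided testing, not to a change of model, and hypotheses 1 and 2 address T2 and T3 separately, where the single-time figure applies.

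The reference cited for 50 is not at hand and might support a different calculation. If so, the inputs that changed need to be stated, because the article states none. Feasibility is a legitimate reason to recruit 50, and the article gives it openly.

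Some stronger inferences are tempting but not supported:
- A reader might take the Bayesian sizes ("87 participants are needed and for a Bayes factor of 5, 99 participants are needed") as contradicting 50. They answer a different evidence criterion, and the effect size behind them is not given.
- A reader might guess that a per-arm figure was taken as a total. Nothing in the text shows this.
- A reader might conclude that 50 suffices only if the baseline–outcome correlation is about 0.7. That applies to a single-time contrast; the pooled effect comes close to 80% at 0.5.
- A reader might infer that the ethics committee was told that 80% power was kept. The article says that the committee approved the change, not what power it was shown, and does not restate 80% after the reduction.

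**Conclusion.** The statement that one-sided testing brings the sample to 50 is wrong as written. On the article's own inputs it brings 98 to 76. At N = 50, one-sided power for f = 0.25 is about 64% with the test used for sizing, and the same for a baseline-adjusted contrast at T2 or T3 alone. The effect detectable with 80% power rises from d = 0.5 to about 0.62.

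These figures rest on correlation 0.5, equal arms and one-sided alpha 0.05. Power is about 79% for a baseline-adjusted effect pooled over T2 and T3, and about 69–73% for a single-time contrast with 56–62 analysed. The first conclusion (76, not 50) is firm. The exact power of the final analysis depends on the contrast chosen.

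**What to change.** In the Sample size section, state that one-sided testing alone reduces 98 to 76, that 50 was set by feasibility, and that 50 gives about 64% one-sided power for f = 0.25 with the stated test (80% for d of about 0.62). Alternatively, if 50 came from other inputs or another model, state them so that the number can be reproduced. If power is quoted for the planned mixed model, name the contrast and the correlation assumed.

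Correct the Discussion sentence on sufficient power to match.

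The cost is a wording correction in two places. No extra patients or data are needed; the stated power becomes less favourable.

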### Interventions

Two standardized treatments with an equal duration will be used before (standardized) exposure therapy: EMDR therapy and supportive counseling. Sessions will be provided face-to-face or if that is not possible by video conferencing.

#### EMDR therapy

This study uses the Dutch EMDR 2021 protocol (Dutch translation of Shapiro’s standard EMDR protocol) [41, 59]. Our case conceptualization strategy will be based upon the central question as to what flashforward drives the patient’s panic disorder. First, the patient’s flashforward will be assessed (i.e., the mental picture that displays the most terrible outcome of a panic attack) and if this is not available to the patient, the patients is helped to create such a flashforward. Second, memories that may have contributed to the onset or persistence of the disorder will be ordered hierarchically based on subjective units of disturbance (SUD) scores. For the processing of patients’ flashforwards with EMDR therapy, the Flashforward procedure will be used [48]. During EMDR sessions, therapists aim to tax working memory maximally. That is, rather than just making eye movements, the therapist induces fast eye movements, tapping, calculations, backward spelling etc. [42–44], an approach that is termed EMDR 2.0 [60]. Multiple targets might be desensitized per session depending on the velocity of SUD decrease. If online treatment is required, a secure online EMDR therapy application (Digital_EMDRapp) will be used as a working memory task [61]. In the app, different reaction time tasks with visual (ball) and auditory (sound) stimuli can be manipulated (pattern, color and speed) and administered by the clinician. This program will be made available free of charge for this project by the company MOOVD.

#### Supportive counseling

Supportive counseling is a non-directive psychotherapeutic procedure that focuses on discussing topics that are relevant to the patient in daily life (e.g., family, daily activities, work). The clinician offers support by attentive listening. A protocol was developed based on the protocols used by Bryant and colleagues (1998) [50] and Boelen and colleagues (2007) [62], to match session duration in the EMDR therapy condition and other non-specific treatment effects, such as therapeutic alliance, time and contact with a therapist [63]. In earlier randomized controlled trials, supportive counseling slightly lowered anxiety symptoms in patients [63], so it has been used as a credible active control intervention. During the supportive counseling case-conceptualization session, threat-related imagery will be assessed the same way as in the EMDR therapy condition, so treatment effects can be attributed to the interventions, instead of the case formulation [64]. Next, a supportive counseling case conceptualization will be made, by making an inventory of potential topics the patient wants to discuss. During the sessions, the patient will be free to change the subject to “whatever topic that’s on their mind” [50, 62]. In supportive counseling, clinicians take an emphatical stance and offer support by using the following steps. (1) Ask an open question: “What do you want to discuss right now?”, (2) deepen the conversation by active listening and open questions, (3) paraphrase and reflect during the conversation, (4) summarize the conversation at the end of the conversation, (5) compliment the patient for the hard work, (6) and end the conversation. In order to study working mechanisms, clinicians are explicitly instructed not to focus on specific CBT procedures (i.e., cognitive restructuring, emotional processing of adverse life events, or behavioral exposure) [64].

#### Exposure therapy

During exposure therapy, the patient is systematically and repeatedly confronted with feared but safe stimuli (e.g., interoceptive cues, objects, situations), with the goal that the patient learns that the anticipated feared outcome does not occur (e.g., getting a heart attack) [8]. Exposure therapy will focus on maximizing threat expectancy violation [8]. For panic disorder, the protocol will be based on the Dutch protocol by Kampman, Keijsers and Hendriks (2017) [65]. It involves psycho-education, interoceptive exposure (e.g., with CO_2_ or physical exercises) and exposure in vivo [66]. To maximize expectancy violation, cognitive techniques prior to exposure are not used, as recommended by Craske and colleagues [8].

### Therapists and training

Therapists participating in the trial will be psychologists, psychotherapists or psychiatric nurse specialists (master degree, advanced mental health qualifications) and have all completed at least a CBT basic course (accredited by the Dutch CBT association) and an EMDR basic course (accredited by the Dutch EMDR association). Therapists are employed in specialized anxiety disorders clinics (Altrecht and Mondriaan). For this study, clinicians will receive four hours of training in exposure techniques (focusing om maximizing threat-expectancy violation), four hours of training in EMDR (focusing on case conceptualization in anxiety disorders and maximizing working memory taxation) and four hours of training in supportive counseling (focusing on non-directive support) by experts in the field. To reduce bias, all therapists will be trained and will participate in all three interventions. To reduce expectancy bias, clinicians will be given the following rationale “EMDR therapy and supportive counseling are both new innovative interventions for panic disorder based on the latest research, but with a different focus. Instead of searching for the best therapy on group level, we will use the latest statistical analysis to unravel what works for whom on an individual level using clinical profiles”. Treatment expectancy of therapists will be assessed. To obtain high treatment quality and to check whether the training was sufficient, supervisors will check case-conceptualizations, session reports, and session recordings.

